### Data analysis and statistical methods

2.10

SPSS 25.0 will be used for statistical analysis, with an ITT methodology. Missing data will be imputed with the last available evaluation. Continuous variables will be presented as mean ± standard deviation (SD) or as median with interquartile range[M (IQR)], while categorical variables will be expressed in terms of frequencies or percentages. Statistical significance will be determined at *p* < 0.05.Baseline anticancer treatment characteristics and clinically relevant concomitant treatments during the trial will be summarized descriptively; if needed, sensitivity analyses or adjusted analyses will be conducted to assess the robustness of the primary outcome.

The proportion of patients with a minimum 3-point reduction on the BFI at week 4 will be assessed using Chi-Square or Fisher’s exact tests for categorical data. For repeated measures, such as changes in BFI scores (week 1,2,3,4,8), Generalized Estimating Equations (GEE) will be employed.

GAD-7, QLQ-C30, leukocyte counts, hemoglobin levels, platelet counts, lymphocyte counts, and CD3+, CD4+, CD8+, and CD4+/CD8+ ratios are examples of continuous variables for which unpaired t-tests or Mann-Whitney U tests will be used for between-group comparisons, as applicable.

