#### Primary outcome

2.7.2

The primary outcome measure is the proportion of patients achieving a reduction of at least 3 points on the BFI at week 4. A responder-based endpoint was selected because it provides a clinically interpretable estimate of the proportion of patients achieving meaningful fatigue improvement. This approach is also consistent with prior symptom-management trial in CRF, in which the BFI has been used not only as a continuous measure of fatigue severity but also to classify clinically relevant improvement or normalization of fatigue status (14). In the present trial, a 3-point reduction was prespecified as an interpretable response threshold based on prior fatigue literature, the 0–10 scaling properties of the BFI, and the preliminary data used for sample size estimation, while continuous changes in BFI scores are also analyzed as secondary outcomes (15). BFI is a subjective and reliable measure assessing the level of fatigue in the past 24h and the impact of fatigue on patients. The questionnaire consists of nine items rated on a 0–10 scale, with a final score range of 0-10. Fatigue is rated as mild (1-3), moderate (4-6), or severe (7-10) (16).

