##### The changes in BFI scores

2.7.3.1

It will be evaluated at weeks 1,2,3,4, 8.

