##### GAD-7

2.7.3.3

The brief anxiety self-assessment tool comprises 7 items, each evaluated on a scale ranging from 0 to 3, resulting in a cumulative score that can vary from 0 to 21. Scores 5–9 suggest the presence of mild anxiety, scores 10–14 indicate moderate anxiety, and scores 15–21 are indicative of severe anxiety (18). It will be assessed at weeks 0 and 4.

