### Sample size calculation

2.9

Based on the preliminary research results, it was observed that 40% of patients in the moxibustion group and 10% in the placebo group exhibited a decrease of at least 3 points on the BFI at week 4. Calculations indicate that the sample size of 58 patients would ensure a study power of at least 80%, with a two-sided significance level of 0.05. To adjust for an anticipated dropout rate of 20%, 37 patients will be finally taken from for each group.

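### One last-value rule for all missing data records dropouts as unchanged on every two-visit outcome and makes the week-4 responder difference depend on when, and from which arm, patients leave

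*Protocol article*

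**What the plan says.** All references are to the protocol article.

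- **Missing data (section 2.10).** "Missing data will be imputed with the last available evaluation". No outcome or visit is exempted. The preceding sentence sets the analysis principle: "SPSS 25.0 will be used for statistical analysis, with an ITT methodology".
- **Expected loss (section 2.9).** The sample size allows for "an anticipated dropout rate of 20" per cent and randomises 37 per arm.
- **Primary outcome (section 2.7.2).** "The primary outcome measure is the proportion of patients achieving a reduction of at least 3 points on the BFI at week 4". Section 2.10 says that it "will be assessed using Chi-Square or Fisher’s exact tests for categorical data".
- **BFI visits (section 2.7.3.1).** "It will be evaluated at weeks 1,2,3,4, 8", with a baseline value in Table 1. Treatment ends at week 4, so week 8 is the only off-treatment assessment.
- **Two-visit outcomes (sections 2.7.3.2 to 2.7.4).** For GAD-7: "It will be assessed at weeks 0 and 4". QLQ-C30, blood counts and T-cell subsets have the same schedule.
- **Sensitivity analyses (sections 2.6.3 and 2.10).** These are conditional, and both mentions concern anticancer and concomitant treatment, not missing data.

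**The concern.** Last observation carried forward (LOCF) replaces an unknown later value with an earlier one and then treats it as measured. What that implies differs by outcome.

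- **Two-visit outcomes.** The only earlier value is baseline, so every patient without a week-4 value enters the between-group test as exactly unchanged.
- **Primary outcome.** A patient who leaves early is judged on a BFI from weeks 0 to 3, before the course is complete, against a threshold meant for week 4. The responder rate in each arm then reflects dropout frequency and timing as well as fatigue.
- **Week 8.** A patient seen at week 4 but not at week 8 is assigned the end-of-treatment score. That assumes persistence, which is what the follow-up visit is there to examine.
- **GEE for repeated BFI.** The model can use the visits that were observed. Filled-in rows add the same bias and understate the uncertainty.

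At stake are the size of the estimated effects and, if dropout differs by arm, the validity of the primary test. The practitioners are unblinded and the arms differ in heat, so equal dropout cannot be taken for granted.

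**Working it through.** **1. The plan's own figure.** Section 2.9 gives its basis: "it was observed that 40% of patients in the moxibustion group and 10% in the placebo group exhibited a decrease of at least 3 points". The unpooled two-proportion formula, two-sided 0.05 and 80% power, gives n = (0.4×0.6 + 0.1×0.9)(1.960 + 0.842)²/0.30² = 28.78, so 29 per arm and 58 in total. Dropout: 29/0.8 = 36.25, so 37 per arm. The stated figures reproduce. At 20% dropout, 0.2×37 = 7.4 patients per arm would carry imputed values.

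**2. Two-visit outcomes.** Assumed, not in the documents: true difference 0.70 SD, common improvement 0.50 SD (so mean improvement 1.20 SD v 0.50 SD), baseline correlation 0.5, dropout completely at random. A dropout contributes zero change, so the expected LOCF difference is (1−d₁)×1.20 − (1−d₂)×0.50, where d₁ and d₂ are dropout on moxibustion and placebo.

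| Dropout, moxibustion / placebo | LOCF difference (true 0.70) |
|---|---|
| 20% / 20% | 0.96 − 0.40 = 0.56 SD |
| 30% / 10% | 0.84 − 0.45 = 0.39 SD |
| 10% / 30% | 1.08 − 0.35 = 0.73 SD |

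With equal dropout the shrinkage is exactly the dropout fraction. In simulation at 20%/20% (8,000 trials, 37 per arm), the t-test gave 0.56 SD with about 60% power under LOCF, and 0.70 SD with about 75% power on observed data.

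**3. Primary outcome.** Assumed: each patient improves linearly to week 4, the week-4 change has SD 1.6, and a dropout's last visit is equally likely to be week 0, 1, 2 or 3. Mean week-4 improvements that give 40% and 10% responders are 3 − 1.6×0.253 = 2.59 and 3 − 1.6×1.282 = 0.95 points. A patient last seen at week k counts as a responder only if the full week-4 improvement would be at least 12/k points. For k = 0, 1, 2, 3 the probabilities are about 0, 0, 1.7% and 19.0% on moxibustion (mean 5.2%), and 0, 0, 0.1% and 2.8% on placebo (mean 0.7%).

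| Dropout, moxibustion / placebo | Moxibustion | Placebo |
|---|---|---|
| none | 40% | 10% |
| 20% / 20% | 0.8×40 + 0.2×5.2 = 33.0% | 0.8×10 + 0.2×0.7 = 8.1% |
| 30% / 10% | 0.7×40 + 0.3×5.2 = 29.6% | 0.9×10 + 0.1×0.7 = 9.1% |
| 10% / 30% | 0.9×40 + 0.1×5.2 = 36.5% | 0.7×10 + 0.3×0.7 = 7.2% |

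**4. Type I error of the primary test.** Suppose there is no true effect, 40% respond in both arms, dropout is 10% on moxibustion and 30% on placebo, and no dropout is counted as a responder (the worst case). The analysed rates are 0.9×40 = 36% and 0.7×40 = 28%, a spurious 8 points. Exact enumeration of the uncorrected chi-square at 37 per arm rejects in 11.4% of trials. If dropouts count as responders at half the true rate (38% v 34%), it is 6.2%. At a common rate of 25%, again with no dropout counted, it is 8.2%. With equal 20% dropout it stays at 5.0%.

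**5. Week 8.** Assumed true differences: 1.5 points at week 4 and 0.5 at week 8.

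- All 20% attend week 4 and miss only week 8: 0.8×0.5 + 0.2×1.5 = 0.70.
- All 20% leave before week 4, timed as in step 3: the mean carried difference is 1.5×(0+1+2+3)/4/4 = 0.5625, so 0.8×0.5 + 0.2×0.5625 = 0.51.

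**The case against.** The best defence is that the trial is short, BFI is taken weekly, and a late dropout's carried score is recent. That stands for BFI and softens the primary-outcome bias. It does nothing for the two-visit outcomes. With equal dropout the primary test also loses essentially no power compared with using observed patients only: pooled power is about 77% at 33% v 8% with 37 per arm, and 77 to 78% at 40% v 10% with 29 or 30 per arm. What remains is a shrunken estimate. The documents give no dropout split by arm, so arm-dependent distortion is a risk, not a demonstrated fact.

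A reader might infer four stronger things that the documents do not support:

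- **LOCF cuts two-visit power from 85% to 60%.** The 85% comes from a baseline-adjusted analysis of observed data. Like for like, with t-tests, the comparison is about 75% v 60%; the other 10 points are due to baseline adjustment.
- **The two-visit bias always runs towards zero.** Step 2 shows 0.73 SD at 10%/30% dropout, above the true value.
- **LOCF hides relapse and overstates the week-8 effect by 40%.** That needs the whole 20% to attend week 4 and then miss week 8, so it cannot be combined with the same 20% leaving before week 4. Even then, a fall from 1.5 to 0.7 would be visible. The masking is partial.
- **Counting missing patients as non-responders avoids the problem.** It gives 0.8×40 = 32% v 0.8×10 = 8% at 20%/20%, and 0.7×40 = 28% v 0.9×10 = 9% at 30%/10%. It shrinks the effect at least as much as LOCF and depends on arm in the same way.

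Nor is this detail that an article may leave to an unseen analysis plan: the article itself fixes the rule.

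**Conclusion.** The concern holds. That dropouts are recorded as zero change on QLQ-C30, GAD-7 and the laboratory outcomes follows from the visit schedule alone. So does the assumption of persistence for anyone missing only week 8.

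The sizes rest on assumptions. With equal 20% dropout at random, two-visit effects shrink by 20%; with unequal dropout the bias can go either way. The primary contrast depends on dropout timing and arm: it falls from 30 points to about 25 at 20%/20% and to about 20 at 30%/10%. The 11% type I error is a worst case and needs more loss on placebo than on moxibustion. The week-8 overstatement lies between about 0.01 and 0.20 points on a true 0.5.

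Severity: should fix. The rule touches every efficacy outcome and no missing-data sensitivity analysis is named. However, under equal dropout the harm to the primary outcome is moderate, and the outcomes affected with certainty are secondary or exploratory.

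**What to change.** Remove the LOCF sentence from section 2.10 and state a method for each type of outcome.

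- **Primary.** Multiply impute week-4 BFI separately by arm from baseline and weeks 1 to 3, then apply the 3-point rule to the imputed scores. Add a prespecified sensitivity analysis that varies the assumption about dropouts by arm. Treating missing as non-response may be one scenario, reported with the caution that it is itself attenuating and arm-dependent.
- **BFI over time.** Fit the longitudinal model to observed visits, without carried-forward rows. A likelihood-based mixed model is preferable to ordinary GEE here, because unweighted GEE on available data generally needs data missing completely at random.
- **QLQ-C30, GAD-7 and laboratory outcomes.** Analyse observed week-4 values adjusted for baseline.

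The change needs new wording and modest extra programming, and no new data. The remaining weakness is reliance on a missing-at-random assumption, which the sensitivity analysis should test for the primary outcome. The wording should be settled before unblinding.

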**Methods:**

This investigation employs a randomized, controlled, single-blinded trial design. A 1:1 random allocation method will be implemented to assign 74 participants to either the moxibustion group or the placebo moxibustion group. All participants will undergo eight sessions over 4 weeks, with sessions occurring twice weekly and lasting for 30 minutes each. Assessments for follow-up will take place at week 8. The primary outcome will be the percentage of patients who show a decrease of at least three points on the Brief Fatigue Inventory (BFI) at week 4. Secondary outcomes will encompass changes in the BFI, Quality of Life Questionnaire-Core 30 (QLQ-C30), Generalized Anxiety Disorder Scale-7 (GAD-7). Meanwhile, Blood cell counts and serum T lymphocyte subsets (CD3+, CD4+, CD8+, CD4+/CD8+) will be measured as exploratory outcomes. In addition, adverse events will be screened and documented throughout the study. An analysis adhering to the intention-to-treat(ITT) principle will be executed.

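### GEE for BFI change at 37 patients per arm: an uncorrected robust Wald chi-square on the group-by-time or joint test would have a true level of about 7.7% to 8.5%, not 5%

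*Protocol article*

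**What the plan says.** All places are in the protocol article.

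- **Data analysis and statistical methods (2.10):** "For repeated measures, such as changes in BFI scores (week 1,2,3,4,8), Generalized Estimating Equations (GEE) will be employed". The same section sets significance at p < 0.05, names SPSS 25.0, follows intention to treat and fills missing values with the last available evaluation.
- **The changes in BFI scores (2.7.3.1):** "It will be evaluated at weeks 1,2,3,4, 8". That makes five post-baseline visits.
- **Primary outcome (2.7.2):** the primary measure is the week-4 responder proportion, and "continuous changes in BFI scores are also analyzed as secondary outcomes".
- **Sample size calculation (2.9):** "37 patients will be finally taken from for each group", "with a two-sided significance level of 0.05".

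The article does not state the variance estimator, the test statistic, the contrast, or any small-sample correction for the GEE model.

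**The concern.** In GEE each patient is one cluster, so this model has 74 clusters, 37 per arm. Two features of the uncorrected robust Wald test then matter. The sandwich variance is biased low in small samples. The chi-square reference also treats that estimated variance as known. With one contrast the two effects together are small. With five visits, a group-by-time test has 4 df and a joint test of group at all visits has 5 df, so a 4×4 or 5×5 covariance matrix has to be estimated from 74 patients, and the error grows.

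GEE is the only method the article names for change in BFI. In Table 1, BFI is the only listed outcome measured at week 8. A claim that the course of fatigue differs between groups would come from this model, and a group-by-time or joint test is a natural way to make it.

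**Working it through.** **Inputs from the article.** n = 37 per arm, 1:1 allocation, five visits, two-sided 0.05. Carry-forward under intention to treat keeps 37 per arm by five visits in the analysis, apart from patients with no evaluation to carry.

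**Assumptions, not in the article.** Means are saturated by group and visit, the sandwich variance is uncorrected (divisor n), and the reference is chi-square. The closed form also assumes normal data. It does not depend on the correlation between visits.

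**The plan's own figure.** The article states that "the sample size of 58 patients would ensure a study power of at least 80" percent, for "40% of patients in the moxibustion group and 10% in the placebo group". With unpooled variance:

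(1.96 + 0.8416)² × (0.4×0.6 + 0.1×0.9) / 0.3² = 28.8, so 29 per arm and 58 in total. Then 29 / 0.8 = 36.25, so 37 per arm.

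The stated numbers reproduce. They concern the responder outcome. The article gives no operating characteristics for the GEE analysis beyond the general 0.05 level.

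**Closed form for the robust Wald test.** Let d be the vector of group differences in visit means and T² the two-sample Hotelling statistic, with ν = 2(n−1) = 72 df. For balanced data the uncorrected sandwich gives

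W = T² × n/(n−1).

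Under the null hypothesis, for a test with p df,

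T² × (ν−p+1)/(pν) follows F(p, ν−p+1).

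The true level is therefore the probability that F(p, ν−p+1) exceeds c × (36/37) × (ν−p+1)/(pν), where c is the 95% chi-square point on p df.

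| Test | p | c | F threshold implied | F df | True level |
|---|---|---|---|---|---|
| One contrast (e.g. week 4 or week 8) | 1 | 3.841 | 3.738 | 1, 72 | 5.7% |
| Group-by-time | 4 | 9.488 | 2.212 | 4, 69 | 7.7% |
| Joint group effect | 5 | 11.070 | 2.035 | 5, 68 | 8.5% |

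**Which cause is larger.** Removing the variance bias (dropping the factor 36/37) but keeping chi-square gives thresholds of 2.273 and 2.091, and levels of 7.0% (4 df) and 7.7% (5 df). Most of the excess comes from the chi-square reference, so correcting the variance alone is not enough.

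**Size of the correction.** The correct 5% points are F(4, 69) = 2.505 and F(5, 68) = 2.350. Converted back to W, they are 10.74 in place of 9.49, and 12.78 in place of 11.07.

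**Robustness to the assumptions.**

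- Simulation of the same statistic used 20,000 null trials per case, two correlation patterns (exchangeable 0.6; 0.8 per week decaying) and three distributions (normal; skewed; rounded and bounded 0–10). It gave 8.0–8.5% (5 df), 7.0–7.8% (4 df) and 5.4–5.9% (1 df). With the F reference the same data gave 4.6–5.1% (5 df) and 4.5–5.2% (4 df).
- Direct GEE fits used an exchangeable working correlation, 1,500 null trials and a Monte Carlo standard error of about 0.7 points. With complete data they gave 7.9% (5 df) and 7.5% (4 df). With 20% dropout and last value carried forward they gave 8.1% and 7.1%. The 1-df average contrast gave 4.8% and 6.9%, each within about two standard errors of 5.7%.
- Model-based variance with the correct working correlation, complete data, gave 5.2% (5 df) and 4.7% (4 df).

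**The case against.** The strongest objection is that the article specifies none of the choices that produce the excess. Robust variance, a Wald chi-square, no small-sample correction and a multi-df contrast must all hold together. A journal article commonly leaves such details to the full protocol or analysis plan, which is not shown. Other ordinary choices nearly remove the effect: a 1-df contrast is at 5.7%, and model-based variance with a correct working correlation, or an F reference, is near 5%. GEE itself is an accepted method here.

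Most of this stands, and it makes the point conditional. What remains is that the method, the number of patients, the number of visits and the 0.05 level are all fixed. A common way of using that method for a group-by-time or joint test misses the stated level by about half or more (7.7/5 = 1.53; 8.5/5 = 1.69).

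Three stronger readings should not be drawn:

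- A reader might infer that the BFI trajectory result will be overstated. The article commits to no such test, and the mechanism affects a p-value, not the estimated mean differences.
- A reader might infer that a claim of persistence to week 8 carries the full inflation. That question is naturally a single week-8 contrast, where the excess is about 0.7 points.
- A reader might apply the calculation to the 29 evaluable patients per arm. That would give 8.5% (4 df) and 9.6% (5 df), but carry-forward under intention to treat keeps 37 per arm, so those figures describe an analysis the article does not plan.

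**Conclusion.** The point holds in conditional form and is minor. If the uncorrected robust Wald chi-square is used, the true level at 37 per arm and five visits is about 7.7% for the group-by-time test and 8.5% for the joint group test, against a stated 5%. This rests on saturated group-by-visit means and, for the exact values, on normality. Simulations under other distributions and correlations, and direct GEE fits with dropout, stay between 7.0% and 8.5%. Only the p-values and interval coverage of a secondary analysis are at issue. The primary responder comparison by chi-square or Fisher's exact test is untouched.

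**What to change.** State which BFI contrast will be tested. For any test with more than one degree of freedom, do one of the following:

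- Keep GEE, with a small-sample-corrected sandwich variance and an F reference. Both parts are needed. This leaves the carry-forward rule unchanged.
- Use a repeated-measures mixed model with group, visit, group-by-visit and an unstructured covariance, and with small-sample degrees of freedom (Kenward-Roger where available). If it is fitted to observed data only, reconcile the missing-data sentence in 2.10 with it.

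In either case include baseline BFI as a covariate. It is already collected. It is not what corrects the level, but it can recover some precision. Confirm that SPSS 25.0 offers the chosen option, or name other software.

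The cost is a sentence or two in 2.10, and slightly wider intervals and larger p-values for a secondary outcome. No change to the sample size or the primary analysis is needed.

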#### Biological specimen exploratory outcomes

2.7.4

Given that CRF has been associated with inflammation and immune dysregulation, exploratory biological outcomes were included to investigate whether symptom changes may be accompanied by changes in host immune status. Peripheral blood cell counts and serum T lymphocyte subsets were selected as clinically accessible exploratory indicators. Exploratory analysis of biological indicators include the following items: (1)Blood cell counts, which include leukocytes, hemoglobin, platelets, and lymphocytes. It will be evaluated at weeks 0 and 4. (2)Serum T lymphocyte subsets, which include CD3+, CD4+, CD8+, CD4+/CD8+. It will be evaluated at weeks 0 and 4.

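### The tests fixed for GAD-7, QLQ-C30 and the blood measures do not adjust for the baseline value already collected, which costs precision on secondary and exploratory outcomes

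*Protocol article*

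**What the plan says.** Section 2.10 (Data analysis and statistical methods) assigns one approach to GAD-7, QLQ-C30, leukocytes, hemoglobin, platelets, lymphocytes and the T-cell subsets: "unpaired t-tests or Mann-Whitney U tests will be used for between-group comparisons, as applicable". No covariate is named, and the scale of comparison (week-4 value or change) is not stated.

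All these outcomes have a baseline measurement. For GAD-7 (2.7.3.3) the article says "It will be assessed at weeks 0 and 4", and QLQ-C30 (2.7.3.2) has the same schedule. For both groups of blood measures (2.7.4) it says "It will be evaluated at weeks 0 and 4". Table 1 agrees.

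The fatigue outcomes are handled differently. Section 2.7.2 states "The primary outcome measure is the proportion of patients achieving a reduction of at least 3 points on the BFI at week 4", analysed by chi-square or Fisher's exact test. For BFI over time the plan reads "changes in BFI scores (week 1,2,3,4,8), Generalized Estimating Equations (GEE) will be employed".

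Adjustment is mentioned only conditionally, for the primary outcome and in connection with anticancer and concomitant treatments: "if needed, sensitivity analyses or adjusted analyses will be conducted to assess the robustness of the primary outcome". Section 2.4 (Randomization) describes no stratification.

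**The concern.** A baseline measurement of the same variable is usually among the strongest available predictors of its week-4 value. A two-sample test on week-4 values leaves that information out. A two-sample test on change scores uses it with a fixed coefficient of 1, which is too large whenever the correlation is below 1 and the SDs are similar. Either way the confidence interval is wider than it need be.

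With 37 per arm and no stratification described, moderate chance differences at baseline are also to be expected on some of the many outcomes. An unadjusted comparison carries part of that difference into the estimated effect. The stake is the precision and interpretability of the secondary and exploratory results, not the validity of the trial.

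**Working it through.** **The plan's own figure.** Section 2.9 gives response rates of 40% and 10%, two-sided 0.05, 80% power, 58 patients, 20% dropout and 37 per group. The unpooled formula gives n = (0.4×0.6 + 0.1×0.9)(1.960 + 0.842)² / 0.3² = 0.33 × 7.85 / 0.09 = 28.8, so 29 per arm and 58 in total. Then 29/0.8 = 36.25, so 37 per arm and 74 in total. The figure reproduces. It rests on the responder outcome alone, so nothing below alters it.

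**Inputs for the continuous outcomes.** From the article: 37 per arm (29 if the anticipated dropout occurs) and two-sided 0.05. Assumed, because the article gives none of them: a true difference of 0.5 SD, equal SDs at both visits, and a baseline to week-4 correlation r of 0.3, 0.5 or 0.7.

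**Variance of the between-group difference**, with week-4 values set to 1: change scores 2(1 − r); ANCOVA 1 − r².

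**Power** from the noncentral t with noncentrality 0.5/√(v × 2/n). For ANCOVA, v carries a small-sample factor 1 + 1/(2n − 4), which is 1 + 1/70 at n = 37. Example at r = 0.5, n = 37: √(2/37) = 0.2325. Week-4 values give 0.5/0.2325 = 2.15 and power 56%. ANCOVA has v = 0.75 × 1.0143 = 0.761, noncentrality 2.15/√0.761 = 2.47 and power 68%.

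| | r = 0.3 | r = 0.5 | r = 0.7 |
|---|---|---|---|
| Variance, change scores | 1.40 | 1.00 | 0.60 |
| Variance, ANCOVA | 0.91 | 0.75 | 0.51 |
| Power, week-4 values, 37 per arm | 56% | 56% | 56% |
| Power, change scores, 37 per arm | 43% | 56% | 78% |
| Power, ANCOVA, 37 per arm | 60% | 68% | 84% |
| Power, week-4 values, 29 per arm | 47% | 47% | 47% |
| Power, change scores, 29 per arm | 35% | 47% | 68% |
| Power, ANCOVA, 29 per arm | 49% | 57% | 74% |

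**Standard errors.** Against week-4 values the ratio is √(1 − r²) = 0.954, 0.866, 0.714, so the ANCOVA SE is 5%, 13% and 29% smaller. Against change scores the ratio is √((1 + r)/2) = 0.806, 0.866, 0.922, so it is 19%, 13% and 8% smaller.

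**Chance imbalance, 37 per arm.** The SE of a baseline mean difference is √(2/37) = 0.23 SD, its 95% range is ±1.96 × 0.2325 = ±0.46 SD, and the probability that it exceeds 0.25 SD in either direction is 28% per outcome. An imbalance δ shifts the unadjusted estimate by rδ on week-4 values and by (r − 1)δ on changes. At δ = 0.46 and r = 0.5 that is 0.23 SD, in opposite directions. Given that imbalance, the false-positive rate is about 13% on either scale. At r = 0.7 it is 21% for week-4 values and 10% for changes. At δ = 0.25 it stays close to 5%. Averaged over all randomizations it is 5%.

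**The case against.** The strongest defence is that the plan uses baseline more than section 2.10 suggests. A reader might infer that every analysis disregards baseline. The article does not support that. The primary responder outcome is defined as a fall from baseline, and the GEE is applied to changes in BFI, so baseline enters both by subtraction. For the GEE what remains is that no baseline covariate is named, a detail that an article may leave to the analysis plan.

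Nor is it established that the t-tests leave baseline out. The abstract says "Secondary outcomes will encompass changes in the BFI, Quality of Life Questionnaire-Core 30 (QLQ-C30), Generalized Anxiety Disorder Scale-7 (GAD-7"), which can be read as change scores for all three instruments. If so, at r = 0.7 the gap to ANCOVA is 84% against 78%, not 84% against 56%. This part of the defence stands, but it does not remove the point. ANCOVA is ahead of change scores too, by 60% to 43% at r = 0.3 and 68% to 56% at r = 0.5. And since the tests themselves are fixed, this is not merely detail left for later.

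A reader might also infer that imbalance invalidates the tests. It does not: under randomization they keep their 5% level, and the distortion is conditional on the imbalance seen.

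Finally, a reader might extend the criticism to the primary test, because a patient entering at BFI 4 must reach 1 or less to respond while one entering at 9 responds at 6. That dependence is real. But "The proportion of patients with a minimum 3-point reduction on the BFI at week 4 will be assessed using Chi-Square or" Fisher's exact test is a valid analysis of a randomized binary outcome and matches the basis of the sample size. The article supplies nothing from which a material gain from adjustment could be shown.

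**Conclusion.** The point holds for the continuous secondary and exploratory outcomes. The fixed tests do not adjust for a baseline that is collected for each of them, and on either possible scale they are less precise than a baseline-adjusted model. Under the assumptions used, with 37 per arm, the power given up at r = 0.3, 0.5 and 0.7 is about 3, 12 and 28 points against week-4 values, and 16, 12 and 6 points against change scores (from unrounded powers). The size depends on the assumed correlation, the 0.5 SD difference, equal SDs and normal-theory tests; the Mann-Whitney option was not computed separately. The sample size, the primary power and the overall type I error are untouched. The change is worth making, but the trial's main conclusion does not depend on it.

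**What to change.** In section 2.10, replace the two-sample comparisons of GAD-7, QLQ-C30, blood counts and T-cell subsets with ANCOVA of the week-4 value on group and the baseline value of the same measure. Report the adjusted difference with its 95% confidence interval, and name in advance the measures to be transformed or analysed by ranks because of skewness. This also settles the unstated scale, since with baseline in the model the group effect is the same whether the week-4 value or the change is the response.

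Enter baseline BFI as a covariate in the GEE.

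Keep chi-square or Fisher's exact test as the governing primary test. If wanted, prespecify a logistic model with group and baseline BFI, reported as a standardised risk difference, labelled supportive only so that there is one primary p-value. With 37×0.4 + 37×0.1 = 18.5 expected responders, about 4 of them on placebo, it should carry no more than that one covariate, with a penalised fit if separation occurs.

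The cost is a change of wording before unblinding, and no extra visits or measurements.
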